### Statistical analysis

#### Sample size calculation

Sample size calculations were based on the ability to detect 10% differences between the three conditions with a power of 0.80 and an alpha of 5%. To calculate the sample size, seven-day point prevalence abstinence at the six- and twelve-month follow-up was taken as the base since it is considered to be the most sensitive and valid measure of smoking cessation [45].

Power calculations were made separately for LSES and HSES groups. For the LSES group we expected that the video condition will result in an 18% quit rate, and the text condition in an 8% quit rate, requiring 176 participants in both conditions. For the HSES group we expected quit rates of 22% in the text-based condition and 12% in the video-based condition, requiring 220 smokers for both conditions.

#### Attrition prevention

Different strategies have been applied in order to prevent high attrition rates. First, respondents completing all questionnaires are eligible to win a price of 100€. Second, the follow-up questionnaires at six and twelve months are brief, only aiming to assess behaviour, readiness to quit smoking, since this strategy has been found to increase participation rates by approximately 8 to 10%. Participants who do not respond to the follow-up measurement at six and twelve months receive two reminders inviting them again to fill in the follow-up measurements. Respondents who still do not react will receive an invitation by e-mail to briefly indicate their current smoking status by indicating whether they have smoked during the last 24 hours, in the last week or in the last months, since this strategy was shown in another study to result in an additional response rate of 8 to10%.

#### Analysis

We will conduct logistic regression analysis at six and twelve months to assess program effects on the main outcome variables. We will further perform linear regression analysis and covariance analysis to assess effects on secondary outcome variables at six and twelve months. We will correct for baseline factors (e.g. demographics, smoking behaviour, attitude, intention) in both types of regression analyses by adding these variables as possible confounders. Interaction effects of experimental condition (text vs. video) and SES will be explored by moderation in the logistic regression analysis since we expect an interaction effect between SES and condition.

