#### Smoking behavior

Smoking behaviour was measured by asking respondents how many cigarettes/shags they smoked per day. Smoking behaviour was converted into an overall score (number of cigarettes a day) [25].

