### Outcomes and biochemical validation

#### Primary outcome measurement

Primary outcome measures of this study measured at six and twelve months after baseline were seven-day point prevalence abstinence from smoking (PPA), continued abstinence and prolonged abstinence. Seven-day point prevalence was defined as not having smoked during the last seven days (measured from follow-up). Continued abstinence was defined as not having smoked since the last quit date, whereas prolonged abstinence took into account a grace period of two weeks [28,44]. During this grace period re-initiating of smoking behaviour after the quit date was not defined as a relapse. All outcome variables were measured according to the definitions in Hughes et al. [28,44]. Smoking during the last seven days and after the personal quit date was coded as relapse (0), whereas non-smoking during the last seven days and since the quit date was coded as abstinence (1).

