#### Secondary outcome measures

Secondary outcome variables measured at six and twelve months after baseline included 24-hour point prevalence abstinence (having smoked during the last 24 hours; 1 = no; 0 = yes), having made a serious quit attempt (not having smoked for at least 24 hours; 1 = no; 0 = yes) and changes in smoking behaviour since baseline measurements [44]. All respondents were further asked to fill out a process evaluation questionnaire at the six-month follow-up to evaluate their experience of the program.

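### Linear regression is named for all secondary outcomes although two of the three listed are binary, and the quit-attempt code runs opposite to the abstinence outcomes (minor)

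*Protocol article*

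**What the plan says.** The Analysis section of the Protocol article divides the models by outcome class. For the primary outcomes: "We will conduct logistic regression analysis at six and twelve months to assess program effects on the main outcome variables". For the rest: "We will further perform linear regression analysis and covariance analysis to assess effects on secondary outcome variables at six and twelve months". No secondary variable is exempted. The next sentence applies baseline adjustment to both kinds of regression, which confirms that a two-way split is meant.

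The section Secondary outcome measures lists three variables:

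- The first, a binary item, is printed as "24-hour point prevalence abstinence (having smoked during the last 24 hours; 1 = no; 0 = yes".
- The second, also a binary item, is printed as "having made a serious quit attempt (not having smoked for at least 24 hours; 1 = no; 0 = yes".
- The third, with no code attached, is given as "changes in smoking behaviour since baseline measurements".

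The first two carry printed 0/1 codes. The third can be treated as continuous, because the section Smoking behavior states: "Smoking behaviour was converted into an overall score (number of cigarettes a day".

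For the primary outcomes, the section Primary outcome measurement gives the direction of coding: "non-smoking during the last seven days and since the quit date was coded as abstinence (1".

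**The concern.** There are two separate defects.

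**Model.** Linear regression and covariance analysis assume one residual variance for all arms. A 0/1 outcome with rate p has variance p(1 − p), which changes with the rate and so with the arm. The choice also splits like from like: seven-day abstinence would be reported as an odds ratio and 24-hour abstinence, the same kind of variable over a shorter window, as a difference in proportions. The two could not be set side by side.

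**Code.** The same pair of labels is attached to two items worded in opposite directions. For having smoked, 1 = no is the favourable state. For having made an attempt, 1 = no is the unfavourable one. At stake is a results table in which one row runs against all the other abstinence-type rows without any signal to the reader.

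**Working it through.** **1. The plan's own figures.** The point rests on no stated number, but the sample size was checked to see whether it is affected. The section Sample size calculation works "with a power of 0.80 and an alpha of 5"%. Its expected seven-day rates are 18% and 8% in the lower-SES group and 22% and 12% in the higher-SES group. The two-sided pooled formula for two proportions is

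n = [1.960·√(2p̄(1 − p̄)) + 0.842·√(p₁(1 − p₁) + p₂(1 − p₂))]² / (p₁ − p₂)²

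- Lower SES, p̄ = 0.13: [1.960·√0.2262 + 0.842·√0.2212]² / 0.01 ≈ 176.4, so 177 per arm (stated: 176).
- Higher SES, p̄ = 0.17: [1.960·√0.2822 + 0.842·√0.2772]² / 0.01 ≈ 220.3, so 221 per arm (stated: 220).

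The stated figures reproduce as numbers per arm. They concern a primary outcome and do not change under the fix.

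**2. Variable type against named model.**

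| Listed secondary outcome | Type | Meaning of 1 | Model named | Model that fits |
|---|---|---|---|---|
| 24-hour abstinence | binary | not smoked (favourable) | linear / covariance | logistic |
| Serious quit attempt | binary | no attempt (unfavourable) | linear / covariance | logistic |
| Change in smoking | cigarettes per day | not applicable | linear / covariance | linear / covariance |

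**3. Effect on standard errors.** The article gives no expected rates for 24-hour abstinence or quit attempts, and no control rate. The seven-day rates are therefore used only as an illustration. The control rate is assumed equal to the lower of the two, and the arms are assumed equal in size.

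Variances: 0.18 × 0.82 = 0.1476; 0.08 × 0.92 = 0.0736.

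*Two equal arms only.* The pooled variance is the mean of the two arm variances, so the standard error of the difference is the same as with separate variances. The two-fold ratio (0.1476 / 0.0736 ≈ 2.0) does no harm here. Simulated type I error of the unadjusted linear test was 0.048 to 0.050 at 176 or 220 per arm, with rates from 8% to 50%.

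*Three equal arms, 18/8/8%.* Pooled variance = (0.1476 + 0.0736 + 0.0736) / 3 = 0.0983. Twice this, before rounding, is 0.1965.

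- Video against text: correct sum 0.1476 + 0.0736 = 0.2212; √(0.1965 / 0.2212) = 0.943, so the standard error is about 6% too small. A nominal 95% interval uses 1.960 × 0.943 = 1.85 true standard errors, which covers about 93.5%.
- Text against control: correct sum 0.0736 + 0.0736 = 0.1472; √(0.1965 / 0.1472) = 1.155, so the standard error is about 15.5% too large. The nominal 5% test then rejects at 1.960 × 1.155 = 2.26, a true level of about 2.4%.

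*Range for video against text.*

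- Control at 5% instead (variance 0.0475): pooled 0.0896, twice that 0.1791; √(0.1791 / 0.2212) = 0.900, so about 10% too small.
- Higher-SES rates, 22/12/12%, for the same comparison: pooled (0.1716 + 2 × 0.1056) / 3 = 0.1276, twice that 0.2552; √(0.2552 / 0.2772) = 0.960, so about 4% too small.

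**4. Effect of the code.** No attempt rates are given, so assume 200 per arm with attempts in 60% against 50%. Under the printed code the linear coefficient is (1 − 0.60) − (1 − 0.50) = −0.10; with 1 = yes it is 0.60 − 0.50 = +0.10. The p-value is about 0.045 under both codes. With 70% against 60% it is −0.10 against +0.10, p about 0.036 under both. Only the direction changes. The bracketed definition of the attempt (at least 24 hours without smoking) does not rescue the code: answering no to that is also the unfavourable state.

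**The case against.** A linear coefficient on a 0/1 outcome is a legitimate risk difference, and the trial was sized on absolute differences of ten percentage points. Fitted values below zero would not by themselves invalidate the treatment contrast. The article is condensed, and the model for each secondary variable is often settled in an analysis plan that is not shown here. These arguments limit the consequence and stand to that extent. They do not remove the point, because the article states one model for every secondary outcome without exception; this is not a detail left open.

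Two stronger readings are tempting, and the document supports neither.

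- A reader might infer that an effective program would be reported as harmful for quit attempts. The value labels are printed, and a negative coefficient on a variable where 1 means no attempt correctly signals more attempts. It misleads only someone who ignores the labels. The code may also be a slip carried over from the preceding item, where the same labels are right.
- A reader might infer from the two-fold variance ratio that inference on these outcomes is badly wrong. The 18% and 8% belong to a primary outcome in the lower-SES group, not to either secondary outcome. With two equal arms the ratio has no effect, and with three the distortion is of the modest size shown above.

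The Analysis section explores the condition-by-SES interaction within the logistic regression. A reader might take its absence from the secondary models as a further error. It is an option for those models and not something the document requires.

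**Conclusion.** The point holds as a minor one. The named model does not fit two of the three listed secondary outcomes, and it separates them from the logistic analysis of primary outcomes of the same nature. If the three arms share one residual variance, pairwise standard errors are off by about 6% (too small, video against text) and 15.5% (too large, text against control) at 18/8/8%. Across the other rates tried, the shortfall for video against text runs from about 4% to 10%. These sizes assume equal arms, no covariates, a control rate the article does not give, and seven-day rates standing in for 24-hour abstinence; they say nothing about quit attempts.

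The quit-attempt code is inconsistent in direction with 24-hour abstinence and with the primary outcomes. It biases neither the size of the effect nor its p-value. The primary analysis and the sample size are unaffected.

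**What to change.** In the Analysis section:

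1. Name logistic regression, with the same baseline covariates as the primary outcomes, for 24-hour abstinence and serious quit attempt.
2. Restrict linear regression and covariance analysis to change in cigarettes per day.

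In the section Secondary outcome measures, code the quit attempt as 1 = yes, 0 = no, so that 1 is favourable for every binary outcome. A condition-by-SES term in the secondary models may be added but is not needed to correct the error.

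The cost is two sentences and one recode. No new data are needed, and the sample size does not change.

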### Additional studies

Additional to the effect study we will conduct two other studies in the same trial, a process evaluation and an economic evaluation, which are described briefly below.

#### Process evaluation

We will conduct a process evaluation to assess the respondents' reactions to the program. Furthermore we will assess differences in evaluation between LSES and HSES smokers. The questionnaire of the process evaluation is based on previously used questionnaires [6,25] and assesses information appraisal of the tailored advice. The concepts attention, comprehension and appreciation of the tailored advice are measured on a five-point scale. Attention is measured by assessing whether the respondents felt that the messages attracted their attention and retained it. Comprehension is measured by asking whether they understood the messages and whether they found them difficult or encountered difficulties with words or passages. Appreciation of the advice is measured by asking whether the respondents liked the messages and whether they found the message personally relevant.

#### Economic evaluation

The economic evaluation involves a combination of a cost-effectiveness analysis (CEA) and a cost-utility analysis (CUA) to analyse whether the e-health program is preferable in terms of cost, effects and utilities from a societal perspective. In the CEA, the incremental cost effectiveness ratio (ICER) is expressed as the incremental costs per additional quitter (measured as 12 months' Point Prevalence Abstinence). In the CUA, the outcome measure is quality-adjusted life years (QALYs), which is based on the EuroQol utility score [30].

## Discussion

The paper describes two multiple computer-tailored smoking cessation programs and the design of an efficacy study that will be conducted to test the effects of the programs on smoking cessation. The computer-tailored e-health approaches are currently tested by Dutch smokers who are motivated to stop smoking. The tailored messages are the same in both conditions; the two conditions only differ in the mode of delivery. One experimental condition uses video-driven messages whereas the other condition uses text-driven messages. The two experimental conditions (video vs. text) will be compared with each other and with a control condition which receives general smoking cessation advice. Furthermore, the effects of the two different multiple tailored smoking cessation programs will be tested among smokers with a lower and higher socio-economic background.

The present study has several strengths. First, it addresses the efficacy of two computer-tailored programs by means of a strong experimental design. A randomized control trial was used to exclude possible biases with regard to assignment of respondents to the different conditions. Allocation of the different conditions was performed automatically with the Tailor Builder computer software.

Second, the intervention is one of the first programs to test video-based messages as a potential new communication strategy for LSES smokers. So far computer-tailored smoking cessation interventions have tended to rely on text-based messages. Several studies however suggest that videos may be more effective in attracting attention and stimulating comprehension, especially in LSES smokers [22].

Third, an important strength of our smoking cessation programs concerns the inclusion of multiple tailored feedback moments. Tailored information has been shown to be more likely to be read, remembered and considered personally relevant. Our study made use of a multiple computer-tailored smoking cessation intervention with different feedback moments. Although previous programs did focus on smoking cessation tailored messages, few of them provided smokers with multiple tailored feedback moments.

Finally, one strategy the study used to collect participants was via the GP setting. The GP is considered as an important access point to many smokers [46]. Advice from GPs is an effective way to help smokers to quit and is seen as valuable by the Dutch patient [47].

There may be limitations to the study. First, the multiple tailoring e-health programs could be too intensive and therefore lead to an increased drop-out rate. Furthermore, the program is only available on the internet, so smokers with no internet access were excluded from the study. Although 90% of Dutch households are equipped with internet access this could still result in selection bias [14].

## Conclusion

A description was provided of the e-health smoking cessation intervention SteunbijStoppen.nl, which was developed especially to attract smokers with a lower socio-economic status. The paper also explained the classification of the study into efficacy and cost-effectiveness of the two programs compared with a control condition and user evaluation. The study results reveal different working mechanisms of multiple computer-tailored smoking cessation interventions. The results will help us to gain more insight into effective strategies to target different subgroups and especially smokers with a lower social economic status. Finally, the results of the study will contribute to the development of future smoking cessation e-health programs. The different behavioural effects of the Steunbijstoppen.nl intervention will be published in other papers.
